### Cost effectiveness analysis

We will perform a cost-effectiveness analysis from a societal perspective. Incremental cost-effectiveness ratios (ICERs) will be calculated by dividing the difference in total costs between the intervention group and the control care group by difference in readmission/mortality rates and Quality Adjusted Life Years (QALYs). The uncertainty surrounding the ICERS will be estimated with non-parametric bootstrapping (5000 replications). The intention to treat principle will be applied to analyse the data. Missing values for cost and effect data will be predicted by multiple imputation.

### Process evaluation

Quantitative data will be collected by using pre-defined process indicators to measure study performance and adherence to the intervention by the patient, CRN, CCRN and PT. Process indicators will be used to study fidelity and adherence to the study protocol. Process indicators are focussed on documentation, communication between healthcare providers, consultation of disciplines, referral to healthcare providers and medication issues. All process indicators will be quantified by nominator and denominator and collected through existing resources. Usual care will be documented to be able to assess the difference between the intervention and control group. In addition, qualitative data will be collected during the intervention by focus groups with healthcare providers and in semi-structured interviews with patients and informal caregivers to evaluate satisfaction with the intervention. These data will be analysed to identify factors that promote or impede future implementation of the CCB care program.

### (Serious) adverse events

Study related adverse events (AE) will be reported when the AE occurs during the comprehensive geriatric assessment and baseline data collection or after discharge when the AE occurs during the home visits by the CCRN or during the physical therapy sessions / self-practice physical therapy sessions by the patients within the intervention period (till 12 weeks post-discharge). After 12 weeks, the intervention has stopped. Therefore, serious adverse events after this period are not expected to be caused by the study and will only be recorded during the annual security reports.

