## Background

Cardiac disease is the leading cause of hospitalization and mortality [1]. In the population of older hospitalized cardiac patients, 20% are readmitted and 10% die within 1 month post-discharge [2]. In addition to cardiac disease, geriatric conditions such as impaired activities of daily living (ADL) (77%), cognitive impairment (42%) and fall risk (30%) are highly prevalent [3]. The assessment of geriatric conditions is not currently part of routine medical evaluation in cardiology. As a result, these conditions are often unrecognized [4, 5] leading to an increased risk of new disabilities, readmission and death [3, 6].

The transition of care in which patients transfer between different settings increases the risk for adverse health outcomes due to inadequate attention to patients’ healthcare needs [7, 8]. For example, the failure to recognize geriatric conditions in older cardiac patients negatively impacts treatments post-discharge, e.g. because of nonadherence to (pharmacological) treatment in cognitively impaired patients [4] or poor participation in cardiac rehabilitation programs because of disabilities, the high intensity of these programs [9, 10], fatigue [11] and difficulties traveling to and from cardiac rehabilitation centers [12, 13]. This is unfortunate since cardiac rehabilitation has been shown to reduce cardiovascular risk factors, readmission and mortality in older cardiac patients [14].

Adequate guidance during hospitalization, during the transition from hospital to home and in the early post-discharge period may potentially reduce the risk of adverse events. Transitional care is a model that aims to continue care when patients transfer between different care settings, with a focus on patients’ needs [15, 16]. Recently, the Transitional Care Bridge program resulted in a 25% (HR 0.75, 95% CI 0.56–0.99, *P* = 0.045) reduction in mortality in acutely hospitalized older patients, by combining a Comprehensive Geriatric Assessment (CGA), an integrated care plan and a transitional care program, including visits during hospitalization and soon after discharge by a community care registered nurse (CCRN) [17]. However, with this case management approach no effects were found on readmission rates and ADL-functioning. We hypothesize that this may be caused by a main focus on case management within the care transition program with a lack of attention for disease management and rehabilitation after discharge.

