### Randomization and blinding

After patients are screened for eligibility and have provided informed consent to a cardiac research nurse (CRN), the baseline assessment will be performed. After the baseline assessment patients will be randomized to the intervention or control group. Stratified block randomization (1:1) will be used with pre-stratification by study site and cognitive status based on the MMSE (15–23 vs ≥ 24). To ensure allocation concealment, a web-based data management program (Research Manager, http://deresearchmanager.nl/nl/home/) [25] and random permuted blocks of variable sizes will be used.

Group assignment will be blinded to patients. They will be informed that the study aim is to study different forms of post-discharge care and will receive only general information about the study protocol according to the postponed informed consent procedure of Boter et al. [26] Patients will be blinded to the aim of the intervention to prevent a potential Hawthorne effect [27, 28]. At the end of follow-up, patients (or their caregivers) will be fully informed about the content of the study intervention and the allocated treatment they received. Healthcare practitioners who execute the intervention cannot be blinded. Outcome assessments will be performed by research nurses who are blinded to the allocated treatment. Statistical analyses will be performed according to a predefined statistical analysis plan (see Statistical Analysis paragraph) by investigators blinded to group assignment.

Due to the minimal expected side effects related to the intervention of the CCB care program a data monitoring committee is not mandatory for this trial.

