### Intervention

The CCB program encompasses three phases of the care process: 1) clinical phase, 2) discharge phase from hospital to home and 3) post-clinical phase after hospital discharge. The intervention consists of three components: 1) case management, 2) disease management and 3) home-based cardiac rehabilitation. Medication management is an important topic in the three phases of the CCB intervention and is part of all three components.

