In Table 2, the home visit schedule is presented, including specific themes during the home visits. The CCRN is allowed to deviate from the home visit schedule if indicated, for example because of changes in patients’ health status. During the home visits, the CCRN will indicate and refer if there is a need for additional care (domiciliary or otherwise) during or after the intervention period. For specific questions related to patients’ health status or medication discrepancies identified during medication reconciliation, the CCRN has access to the cardiac team of the hospital, the general practitioner (GP), pharmacist according to local communication routes or protocols of the hospitals. During the home visits the CCRN observes signs and symptoms of actual or potential drug-related problems (DRP), such as side-effects and inappropriate medication use (e.g. nonadherence) by using a recently developed instrument (Additional file 2. Adapted Red Flag instrument) based on the Red Flag instrument by Sino et al. [31] The observed problems are documented by the CCRN in the Adapted Red Flag instrument and evaluated by the pharmacist-investigator who has identified DRP and proposed suitable solutions. Subsequently the CCRN discusses these DRP and proposed solutions with the responsible healthcare providers.

The PT provides two home-based cardiac rehabilitation sessions per week during the first 6 weeks post-discharge. This program is based on therapy advices according to the Dutch multidisciplinary guideline of cardiac rehabilitation [32]. Depending on the patient’s functional status a stepwise graded exercise approach will be followed, starting with low intensity functional rehabilitation (class IV or higher on the Specific Activity Scale [33]) to the Metabolic Equivalent of Task level [34] (MET-level) needed for their goals and desired activities, as described in the rehabilitation plan. Exercise therapy will be adapted to comorbid diseases according to current guidelines. Within the last 2 weeks of the rehabilitation program, patient’s functional status will be evaluated. The CCRN and PT work in close collaboration during the intervention to tailor care and to evaluate progress. They have a joint home visit in the first week after discharge to verify and agree on the integrated care plan in relation to patients’ priorities.

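### Up to 12 weeks after discharge, adverse event reporting is tied to intervention contacts, so it is absent in controls, omits harms arising between contacts and cannot be compared between arms

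*Protocol article*

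**What the plan says.** The section on (serious) adverse events defines two reporting settings. The first: "Study related adverse events (AE) will be reported when the AE occurs during the comprehensive geriatric assessment and baseline data collection". The second: "after discharge when the AE occurs during the home visits by the CCRN or during the physical therapy sessions", with self-practice sessions included, bounded at 12 weeks post-discharge. It then says that the intervention has stopped by that point, so that later serious adverse events are not expected to result from the study and are recorded only in the annual reports. No arm is named for those later events.

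Four other sections bear on this:

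- **Randomization and blinding:** "After the baseline assessment patients will be randomized to the intervention or control group". The same section considers a data monitoring committee unnecessary because few side effects are expected.
- **Table 2 and Usual care:** home visits by the community nurse (CCRN) and the home-based exercise sessions belong to the intervention arm.
- **Intervention:** "Medication management is an important topic in the three phases of the CCB intervention and is part of all three components". Phase 3 describes how this works. The nurse documents a possible drug-related problem and the pharmacist-investigator proposes a solution. Then: "Subsequently the CCRN discusses these DRP and proposed solutions with the responsible healthcare providers".
- **Phase 3, last paragraph:** a patient readmitted to a participating hospital and ward during the 12 months of follow-up receives the program again, without the exercise component.

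**The concern.** Within the first 12 weeks, a study-related event becomes reportable by where and when it happens. Those places and times are almost all features of the intervention itself, so the arms differ in whether an event can be reported at all.

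Two things are at stake. First, a table of adverse events by arm would show whatever was seen in the intervention arm against a structural zero in controls. It would say nothing about excess harm, and it would still understate the intervention-arm total. Second, the decision to run without a monitoring committee rests on an expectation of slight side effects, and this reporting rule is too narrow and one-sided to check it.

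**Working it through.** The article gives no figure on this point, so the check sets the sections side by side.

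**Step 1. Reporting settings by period and arm** (adverse event section, read with Randomization and blinding, Table 2 and Usual care):

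| Period | Setting named in the rule | Intervention | Control |
|---|---|---|---|
| In hospital, before randomization | Geriatric assessment and baseline data | Yes | Yes |
| In hospital, after randomization | None | No | No |
| After discharge to 12 weeks, at contacts | Nurse home visits; exercise or self-practice sessions | Yes (2 settings) | None (0 settings) |
| After discharge to 12 weeks, between contacts | None | No | No |
| After 12 weeks | Serious events, annual reports | Not restricted by arm | Not restricted by arm |

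Up to 12 weeks, the count of post-randomization settings is 2 against 0. The only setting that both arms share in that period comes before randomization and cannot reflect the program.

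**Step 2. Program components against the windows.**

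- *In-hospital part after randomization.* The integrated care plan, the geriatric consultation and the pre-discharge nurse visit fall after the baseline window and before the post-discharge one.
- *Medication management.* A change follows a chain from nurse to pharmacist to responsible provider. A reaction to that change may well begin between visits, although the article does not say when reactions occur. If it does, it is outside the rule.
- *Exercise.* Harm during a session or self-practice is inside the rule. Harm that appears afterwards is outside it.

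**Step 3. What both arms supply anyway** (Table 3; Primary outcome; Secondary outcomes):

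| Item | 3 months | 6 months | 12 months |
|---|---|---|---|
| Death, readmission, emergency visits, falls | Yes | Yes | Yes |
| Medication side effects or difficulties | No | Yes | No |
| Dizziness, angina, palpitations, pain | No | Yes | No |

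Serious consequences are therefore collected in both arms at all three times. The medication side-effect question is not asked at 3 months, the contact closest to the end of the scheduled program.

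**Step 4. The 12-week boundary.** The adverse event section treats the program as finished at 12 weeks. Phase 3 provides for repeating it, apart from exercise, on readmission at any time in 12 months. A patient readmitted in month 5 would receive program visits well after the first 12 weeks. The reason given for not expecting study-caused serious events after 12 weeks does not hold for such a patient. The article does not say whether the 12 weeks restart at a later discharge.

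Readmission is not a rare exception. The planning figures put readmission or death by 6 months at 31.5% in the intervention arm: 0.315 × 250 = 78.75, or about 79 patients. How many would receive a repeat program cannot be derived. That total includes deaths, events within the first 12 weeks and admissions elsewhere, and it leaves out readmissions after 6 months.

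**The case against.** The strongest reply is that little of importance is lost. Four parts of it deserve an answer.

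1. *Serious harm is compared by randomized arm.* This stands. Unplanned readmission or death is the primary outcome, with 3- and 12-month versions as secondary outcomes and blinded assessors. On the planning figures, the 6-month comparison would rest on about 0.44 × 250 = 110 control and 79 intervention patients with an event. A reader might infer from the adverse event section that delayed harms go unrecorded, or that the trial can support no statement on safety. Table 3 and the primary outcome contradict both inferences. What remains is narrower: these events enter as outcomes, and the adverse event section gives no route for considering them as possible harms of the program.

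2. *The rule covers study-related events, so a link to study procedures is natural.* This stands in part. Relatedness is a condition of the rule, but so is the setting. A related event that begins between contacts meets the first condition and fails the second.

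3. *The nurse looks for side effects at home visits and documents drug-related problems.* True, and a persisting reaction could be seen at the next visit. However, this record exists in one arm only and is not described as adverse event reporting. Reading the rule generously, so that anything noticed at a visit counts, would widen the difference between arms. Controls may be referred to center-based rehabilitation, but the rule is framed by the intervention period, and the article expects few such referrals.

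4. *This is a condensed article.* The full protocol may describe more. The point rests on a rule that the article states, not on something it leaves out.

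**Conclusion.** The point holds as a defect in the adverse event rule. Up to 12 weeks post-discharge, controls have no post-randomization reporting setting and the intervention arm has two. The in-hospital program after randomization is in no window, and drug or exercise harms between contacts are not reportable as adverse events. Adverse event counts are therefore not comparable between arms and cannot test the expectation of slight side effects. The loss falls mainly on non-serious or delayed harms and on the attribution of serious ones, because death, readmission, emergency visits and falls are collected in both arms.

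The share of events missed cannot be estimated from the article. A reader might try to gauge it from contact hours as a fraction of 12 weeks. Session length and self-practice time are not given, and clock time does not measure harms missed.

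The statement that the program stops at 12 weeks and the provision to repeat it on readmission contradict each other and must be reconciled.

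The conclusion assumes that the rule is applied as written. It is worth correcting and does not affect the primary efficacy comparison.

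**What to change.** 1. Replace the setting-based rule with one time window that is the same in both arms: randomization to 12 weeks post-discharge.
2. At the existing 3-month telephone call by the blinded research nurse, ask the medication side-effect question already used at 6 months, plus one question on injury or other harm. Use the same wording in both arms.
3. Tabulate the answers by randomized arm as safety outcomes, together with the falls, emergency visits, readmissions and deaths already collected. The readmission and emergency-visit questions look back six months, so at this call events need dates to separate those after randomization from those before.
4. Report events noted at nurse or therapist contacts and during self-practice separately, as intervention-arm data that are not compared between arms.
5. Limit relatedness review to the intervention arm, or do it blinded to allocation. Relatedness to the program has no clear meaning for controls, and judging it openly could require knowing the allocation.
6. Reconcile the adverse event section with the repeat-program provision in Phase 3, and state what is reported during a repeat.

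Cost: a protocol amendment, one or two more questions at an existing call, and more events to log, most of them due to underlying disease. No new visits are needed.

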### Phase 3: Post-clinical phase

After discharge home, the CCRN and PT continue care at home. The focus of these visits is in the first month post-discharge since this is when patients are at highest risk for readmission, mortality and functional decline [2, 3]. The CCRN visits the patient four times post-discharge; within 2 days, at 1, 3 and 6 weeks and if needed one more visit within 12 weeks post-discharge. During all home visits, the CGA, the integrated care plan and patients’ current medical condition is evaluated. During the first home visit medication reconciliation is performed by the CCRN to obtain the most accurate possible list of a patient’s current medications [29, 30]. This is done by comparing all the medications that the patient is taking (including over-the-counter drugs, herbals and vitamins) to those listed in the provided medication records (medication overview from the community pharmacy and the discharge summary from the hospital). Within 48 h after discharge the discharge summary, which contains an overview of the medications at discharge, reasons for changes in medication and results of diagnostic tests is sent from the hospital to the CCRN and pharmacist who is part of the research team.

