In case of readmissions to participating hospitals and wards during the study follow-up of 12 months, patients will repeatedly receive the CCB program with exception of the rehabilitation exercise component. This is due to the limit on physical therapy sessions funded by Dutch healthcare insurance policies.

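### Adverse-event reporting after discharge ends at 12 weeks because the intervention is said to be over, but the program can be delivered again at any time in the 12-month follow-up

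*Protocol article*

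**What the plan says.** Two sections of the protocol article bear on this point.

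**(Serious) adverse events.** Study-related events are reported if they occur during the geriatric assessment and baseline data collection. After discharge they are reported if they occur at community nurse (CCRN) home visits or during supervised or self-practice physical therapy, "within the intervention period (till 12 weeks post-discharge". The reason for the limit is "After 12 weeks, the intervention has stopped". The consequence drawn is that "serious adverse events after this period are not expected to be caused by the study and will only be recorded during the annual security reports".

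**Phase 3: Post-clinical phase.** Home visits after a discharge are planned "within 2 days, at 1, 3 and 6 weeks and if needed one more visit within 12 weeks post-discharge". The same section then provides for repetition. The trigger is a new admission to a participating site and ward at any point in the year of follow-up, and the rule is that "patients will repeatedly receive the CCB program with exception of the rehabilitation exercise component".

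**The concern.** The 12-week cut-off has one stated reason, and another section of the same article contradicts it. For a patient who is readmitted to a participating ward and receives the program again, the intervention has not stopped at week 12 after the index discharge.

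The repeat course includes a contact that the safety section itself treats as reportable, namely the CCRN home visit. An event at such a visit is reportable in week 6 after the index discharge but, as written, not in week 30, although the activity is the same. Medication management also remains, because the Intervention section places it in all three phases and components.

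At stake is how complete the safety account of the intervention arm is. The trial has no data monitoring committee; the section on randomization and blinding justifies this by the minimal side effects expected. The safety claim therefore leans on event reporting and attribution, and for repeat delivery after week 12 both are weakened.

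**Working it through.** The plan gives no figure on this point to reproduce. The check sets the sections side by side and works out the timing.

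**1. Is the stated reason true for every patient?** The safety section treats week 12 after discharge as the end of the intervention. This matches the length of one course, since the optional last visit falls within 12 weeks of a discharge. The post-clinical section allows a further course after a readmission at any time in the 12-month follow-up. The reason therefore holds for patients with a single course and fails for patients with a later repeat.

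**2. How late can repeat contact occur?** Let *r* be the week of re-discharge, counted from the index discharge. If the visit schedule is applied anew, the last scheduled visit is at *r* + 6 and the optional-visit window closes at *r* + 12.

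| Re-discharge, week *r* | Last scheduled visit | End of optional-visit window |
|---|---|---|
| 1 | 7 | 13 |
| 4 | 10 | 16 |
| 12 | 18 | 24 |
| 26 | 32 | 38 |

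The optional-visit window passes week 12 for any *r* above 0. The last scheduled visit passes it when *r* + 6 > 12, that is, for *r* above 6. From *r* = 12 on, the whole post-discharge part of the repeat course lies after the cut-off.

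**3. How much of follow-up is exposed?** Taking 12 months as 52 weeks and ignoring the short time from randomization to discharge, 52 − 12 = 40 weeks, and 40/52 = 77%. This is calendar time in which repeat delivery is possible. It is not a share of patients.

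**4. What is lost after week 12, setting by setting?**

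- *Repeat CCRN home visits:* non-serious study-related events fall outside reporting. Serious events go to the annual reports with the stated expectation that the study did not cause them.
- *Exercise sessions:* nothing is lost through repetition, because the repeat course omits them.
- *Geriatric assessment:* the 12-week limit is attached to the post-discharge clause, so an event during a repeat assessment can be read as still covered.

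**5. Does it touch the efficacy analysis?** No. The sample size (235 per group before loss to follow-up) and the primary composite at 6 months take no input from the safety-reporting window.

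**The case against.** Several points can fairly be made on the other side.

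*The 12 weeks may restart.* The post-clinical section uses 12 weeks as the length of the program after a discharge, so the reporting period could be read as starting afresh at each discharge followed by program care. That reading would close the gap. The safety section does not state it, however, and the sentences that follow read as one fixed end. If a restart is intended, one clause would settle the matter. A full protocol not shown here may contain more detailed safety rules, but the contradiction lies in what this article does state.

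*Harms are not lost altogether.* A reader might infer that all harms after week 12 go unreported. The document does not support that. Serious events are still recorded in the annual reports. Mortality, readmission, emergency visits and falls are collected to 12 months, and medication side effects at 6 months (Table 3). What these sources do not provide is reporting of non-serious study-related events at repeat visits, or attribution of serious ones to the study.

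*The repeat course is narrower than the first.* A reader might infer that every readmission triggers a complete second course. Repetition applies only to participating hospitals and wards and omits exercise, which removes the physical therapy settings named in the safety section. This stands and limits the point.

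*The wording is an expectation.* The text says "serious adverse events after this period are not expected to be caused by the study". It does not say that later events cannot be study-related, so attribution is discouraged but not excluded.

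**Conclusion.** The contradiction is real and affects safety reporting only. For patients who receive a repeat course after week 12, the ground for ending post-discharge reporting is false. Following the rule as written omits non-serious study-related events at repeat CCRN visits and treats serious events as unrelated on a wrong premise. The conclusion assumes that the 12 weeks run from the index discharge, which is the more natural reading but not the only possible one.

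The number of patients affected cannot be computed, because the article gives no rate of readmission to participating wards after week 12. A reader might infer a figure of several dozen from the planning risk. With a constant hazard of −ln(0.685)/6 = 0.0631 per month, the intervention-arm risk is 16.0% by 12 weeks and 53.1% by 12 months. The difference is 37.1%, and 0.371 × 250 = 93 first events.

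To get to patients, one must then assume what share of these events are readmissions and what share of readmissions are to participating wards. With 50% and 25% the result is 93 × 0.50 × 0.25 = 12. With 90% and 75% it is 93 × 0.90 × 0.75 = 63. Neither share is in the document. The constant hazard also fits poorly with the article, which places the highest risk in the first month and cites 20% readmitted and 10% dead within one month in older cardiac patients. The count should not be relied on, and the point does not need it.

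Nor does the document support a claim that patients re-exposed late are sicker than those readmitted early.

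**What to change.** Reconcile the safety section with the repeat-delivery paragraph of the post-clinical phase:

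1. State which discharge starts the 12 weeks, and that the reporting window applies to each period of program delivery, up to 12 weeks after each discharge followed by program care.
2. Confine the statements that the intervention is over, and that later serious events are not expected to be study-related, to patients who are not receiving a repeat course.

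This concerns reporting only and takes no position on whether or how the program should be repeated. The cost is a few lines of protocol text and some additional event reporting by the community nurses already making the repeat visits. Sample size, randomization and the primary analysis need no change.
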